### Data collection tools

The impact evaluation includes child-, caregiver-, household-, CBCC- and village-level data collection (Table 4). The household questionnaire collected data at the household level as well as for each relevant household member separately (main caregiver and all children in reference age groups).

**Table 4 Tab4:** Survey questionnaire modules

Questionnaire	Module	Description
CBCC	Location and access	Identification, location
	Infrastructure	Physical infrastructure, including learning space, water and sanitation, cooking and storage facilities
	Staff	Staff roster, education and training
	Curriculum and services	Quality of CBCC activities and related services
	Caregivers health and nutrition knowledge	Knowledge related to optimal infant and young childcare and feeding practices
	Health and hygiene practices	Health and hygiene practices of CBCC staff
	Meal provision	Meal quality, portion sizes, meal planning, management and distribution
	Food procurement	List of food procured/sourced by the CBCC
	Garden land	Land used by CBCCs, including ownership and use, size of the plot, crops planted, input and labour for each plot
	Garden production	Crop production and use
	Garden sales	Crop sales, volumes and prices
	Food storage	Food storage infrastructure and practices
Household	Roster	Listing of demographic characteristics of household members
	Dwelling characteristics and assets	Basic features of the household’s primary dwelling place, including infrastructure, access to water and electricity
	Assets	Assets owned (by men and women separately)
	Land	Land owned and used by household’s women and men, including ownership and use, size of plot, crops planted, labour for each plot
	Agricultural production	Crop production and use
	Agricultural marketing	Crop sales, volumes, prices,
	Agricultural storage	Storage volumes and management
	Farm investments	On-farm investments and labour
	Farming practices	Pre- and post-harvest practices
	Livestock	Livestock holdings, revenue and costs, women ownership
	Employment and business enterprise	Non-farm sources of income (including employment), costs, male and female members
	Shocks	Unexpected events that may have influenced household’s wellbeing and responses taken by household
	Food security	Household vulnerability with respect to food frequency
	Food expenditures	Food expenditures and quantities consumed at household level
	Non-food expenditures	Expenditures on household items, clothing and personal expenditures over the last month
Caregiver	Caregiver’s health and hygiene	Health- and hygiene-related questions
	Caregiver’s health and nutrition knowledge	Knowledge related to optimal infant and young childcare and feeding practices
	Caregivers IYCF practices	Infant and child feeding practices
	Childcare practices	Childcare practices, including support for learning and stimulation
	Women’s time allocation	Women’s use of time, perceptions on women’s time use
Child	Child health	Child immunisation history and health-related questions
	Dietary assessment	Interactive 24-h recall on food intake for children aged 3–5 years
	Anthropometry	Physical measurements of all children and their parents
	Development	MDAT scores (fine and gross motor, language and social domains)

*CBCC* community-based childcare centre, *IYCF* Infant and Young Child Feeding, *MDAT* Malawi Development Assessment Tool

### Methods of analysis

The randomised design allows for the identification of causal impacts of interventions using comparisons of mean outcomes between the randomised treatment arms at end line. The analysis will follow the intention-to-treat approach as protocol and as treated, using econometric analysis for all the relevant outcomes of the intervention. Following [22], impact will be assessed using both a ‘difference-in-difference’ (DID) estimator and a single difference analysis of covariance (ANCOVA) model. Depending on the level of clustering of the outcome, we will employ multilevel regression models that account for the hierarchical nature of the data [23]. Multilevel models, also known as mixed-effects models, use both fixed effects (covariates) and random effects in at-school and household levels.

The DID estimate is calculated as the average change in the outcome of interest in the treatment arm minus the change in outcome in the control group. A difficulty of DID analysis involves serial correlation [15] resulting from unobserved factors affecting the outcomes that are themselves correlated over time. Serial correlation affects estimated standard errors and can lead to erroneous acceptance or rejection of null hypotheses but not the estimation of the effect size of the intervention. It may, therefore, lead to erroneously finding or not finding a statistically significant impact of the intervention. This problem can be addressed by calculating clustered standard errors [24]. Clustered standard errors will also be employed in all cases in which correlated outcomes are observed within the same unit of analysis. The analysis of covariance (ANCOVA) estimator has been shown to provide a more efficient estimate of programme impact when autocorrelation of outcomes is low [22].

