### Random assignment and manipulation of treatments

The 60 communities were randomly assigned to one of two treatment arms:Control group: communities with CBCCs supported by Save the Children’s ECD programme with no additional nutritional or agricultural supportIntervention group: communities with CBCCs supported by Save the Children’s ECD programme with additional nutritional and agricultural support

The integrated intervention package will be implemented in 30 of the 60 rural communities after the baseline survey and extended to the control communities after the end-line survey. There are several reasons why the control group in this case is not a control without intervention. The Government of Malawi is committed to scaling-up the ECD quality improvement across all CBCCs and an impact evaluation on the cost-effectiveness of different ECD quality improvement strategies is underway.^2^ The proposed evaluation complements the ongoing work by examining the relative impact and costs of alternative implementation models, focussing on how to enhance participation in the CBCCs and, at the same time, supporting the nutrition of children at a critical age in their development.

The 60 CBCCs were randomly selected in two stages from a pool of 235 CBCCs in 47 clusters currently assisted by Save the Children in Zomba. Due to the clustering of the CBCCs around primary schools, the list of 235 CBCCs was screened to flag clusters where more than one CBCC was being assisted. Twenty-six clusters were excluded from the first stage of randomisation to minimise possible contamination. An additional 10 CBCCs were dropped as they had ongoing activities. The 20 clusters were then randomly assigned to two groups of 10 clusters, where the randomisation was stratified geographically by traditional authority areas. In the second stage of randomisation, within each cluster, three CBCCs were then selected at random for the study. As six clusters had fewer than three CBCCs available for the study, in order to select a full sample of 30 CBCCs per treatment arm, additional CBCCs were randomly selected from three clusters (Gologota, St. Pius and Machereni).

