### Sample sizes

Initial power calculations and resource availability had suggested the adoption of a sample with 30 clusters (communities) per treatment arm with 20 households in each cluster to identify reasonable treatment impacts of the intervention on the primary study outcomes. Data for power calculations was obtained from the 2010 Demographic and Health Survey (DHS) survey. We calculated means, standard deviations and intracluster correlation coefficients (ICCs) for rural children in Malawi. For Dietary Diversity Score (DDS), the mean and standard deviation for rural children aged 0–5 years were estimated to be 2.5 and 1.03, respectively. The ICC was 0.01. Plots of the standardised minimum detectable effect size (MDES) against the number of clusters assuming a sample of 25 children measured in each community (cluster size), consistent with 20 household interviews per community and considering that several children may end up not being tested, showed that only a marginal gain can be obtained by expanding the sample beyond 20 as power is mainly driven by the number of clusters [21] (see Fig. 2 for example simulations of MDES versus number of clusters with high and low ICCs).

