**Fig. 3 Fig3:**
[figure not shown]
Impact pathways for the intervention on child nutrition and development (Fig. 3). (Source: adapted from [28])

After preliminary design visits to the targeted communities, the sampling strategy was modified to account for the implementation approach adopted by Save the Children, involving the clustering of CBCCs around surrounding primary schools. As a result, the cluster, or unit of randomisation was the primary school cluster that included a number of different CBCCs, rather than the CBCC itself. Adjusting for ICCs at the primary school cluster level, where 60 CBCCs were clustered into two groups of 15 primary school clusters, would provide 80% power to detect a 0.24-SD difference between treatment groups at the 5% level of significance (Table 3).

**Table 3 Tab3:** Sample sizes

	Primary clusters	Communities/CBBCs	Households with children of target age	Children (0–5 y)	Children (3–5 y)
Control	15	30	600	936	648
Intervention	15	30	600	936	648
Total	30	60	1200	1872	1296

Note: Number of children estimated based on demographic data from the Demographic and Health Survey (DHS), 2010

*CBBCs* community-based childcare centres

The sampling of households was conducted through a census within a certain catchment area for each CBCC including information on the target age groups living within each household. Households with children aged 3–5 years were then randomly selected for participation in the survey.

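### Clustered standard errors and multilevel models are named with no few-cluster adjustment, although only 20 school clusters of unequal size are described as randomised; conventional versions would test at about 6% to 10% instead of 5%

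*Protocol article*

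**What the plan says.** Methods of analysis plans difference-in-difference and ANCOVA estimates, multilevel models with random effects at school and household level, and clustered standard errors. After warning that serial correlation can produce false findings, it says that "This problem can be addressed by calculating clustered standard errors". The same device is then extended to every case of correlated outcomes within a unit. The article does not give the clustering level, the form of the variance estimator, the reference distribution, the degrees of freedom, or whether mixed models are fitted by ML or REML.

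On the design, Sample sizes says that "the cluster, or unit of randomisation was the primary school cluster that included a number of different CBCCs, rather than the CBCC itself". Random assignment and manipulation of treatments gives the number: "The 20 clusters were then randomly assigned to two groups of 10 clusters". It also shows that sizes are unequal. The target was three CBCCs per cluster, but "As six clusters had fewer than three CBCCs available for the study", and so "additional CBCCs were randomly selected from three clusters" to reach 30 CBCCs per arm.

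The power statement uses a different number, in which "60 CBCCs were clustered into two groups of 15 primary school clusters". Table 3 repeats it: 15 per arm, 30 in total.

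**The concern.** Conventional cluster-robust errors are justified when the number of clusters is large. With 10 clusters per arm, the unadjusted sandwich estimator is too small on average, and unequal sizes make this worse. Maximum likelihood also underestimates the between-cluster variance. A normal critical value ignores that about 18 degrees of freedom are available for the treatment contrast. P-values are then too small and intervals too short.

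The excess per test is modest, but it recurs. Table 2 has four primary domains, some with several indicators, the article plans extensive subgroup analyses, and the results are meant to inform national scale-up.

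**Working it through.** **The plan's own figures.** The article gives no type I error other than the nominal 5%. Its power figure, 0.24 SD, matters here only for the ICC it implies. The detectable effect is (1.960 + 0.842) × √(2·DE/n), with DE = 1 + (m − 1)·ICC. For 600 households per arm in 15 clusters, m = 40. The only ICC given is for dietary diversity: "The ICC was 0.01". Then DE = 1.39 and the result is 0.191 SD, not 0.24. Reaching 0.24 needs a school-cluster ICC of about 0.031 to 0.036 (depending on whether 40, 43.2 or 50 observations per cluster are used), which is not stated. The figure therefore cannot be confirmed, and a range of ICCs is used below.

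**Cluster sizes implied by the text.** There are 60 CBCCs in 20 clusters. Six clusters fall short and three are topped up, which leaves 11 with three each (33). Assuming one or two CBCCs in each short cluster, the six hold 6 to 12. The three topped-up clusters then hold 60 − 33 − 12 = 15 to 60 − 33 − 6 = 21, an average of 5 to 7 each. The two ends are:
- mild: 11×3, 3×5, 6×2; variance (3·2² + 6·1²)/20 = 0.9, CV = 0.95/3 = 0.32
- harsh: 11×3, 3×7, 6×1; variance (3·4² + 6·2²)/20 = 3.6, CV = 1.90/3 = 0.63

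Equal sizes are excluded by the text and serve only as an analytic check.

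**Equal-size check.** With 10 equal clusters per arm, the unscaled sandwich variance is 9/10 of the unbiased one, so the statistic is t(18)/√0.9.
- Unscaled, normal reference: P(|t18| > 1.96·√0.9) = 7.9%
- Scaled by G/(G−1) = 20/19, t(19) reference: P(|t18| > 2.093·√(0.9·20/19)) = 5.7%
- Unbiased variance, normal reference: P(|t18| > 1.96) = 6.6%

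**Unequal sizes, null simulation.** Settings: 20 clusters, 30 CBCCs per arm, 20 households per CBCC, ICC 0.01, 0.03 and 0.10, clustering on the school cluster, two-sided, no covariates or strata, 40,000 runs per setting.

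| Method | CV 0.32 | CV 0.48 | CV 0.63 |
|---|---|---|---|
| Unscaled sandwich, z | 8.2-9.1% | 9.2-9.4% | 10.0-10.6% |
| G/(G−1) scaled, z | 7.5-8.3% | 8.4-8.6% | 9.3-9.9% |
| G/(G−1) scaled, t(19) | 6.0-6.5% | 6.7-6.9% | 7.4-7.9% |

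A separate simulation under unequal sizes gave 6.4%-8.1% for the scaled t(19) version and 7.9%-10.8% for z-referenced sandwich errors.

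**Mixed models.** These used 4,000 runs per setting with equal sizes or a moderate pattern (1,2,2,3,3,3,3,3,5,5 in each arm), with residual variance taken as known. REML with Wald z rejects at 6.2%-7.3% and ML with Wald z at 7.4%-8.7%.

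**With a few-cluster method.** A t test on cluster means gives 4.7%-5.1%, REML with t(18) gives 4.6%-5.4%, and a jackknife-type (CR3) sandwich with t(18) gives 4.4%-5.4%.

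**If there were 30 clusters.** With two CBCCs in each, the unscaled sandwich with z gives 6.6%-6.9% and the scaled version with t gives 5.1%-5.4%.

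**The case against.** The strongest objection is that this is missing detail rather than an error. The article is condensed and the analysis plan is not shown; variance corrections and degrees of freedom are commonly settled there. Clustered errors and mixed models are compatible with every correction recommended below, so nothing in the article would need to be withdrawn. The quoted sentence is also written about serial correlation in the difference-in-difference analysis, not about the number of clusters.

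Much of this stands. A reader might infer that the plan commits to uncorrected errors with normal critical values, or that its tests will in fact run at 7% to 10%. The documents do not support either reading. They fix no sandwich variant, no reference distribution and no ML or REML choice. The common scaled version with t(19) stays at 6.0%-6.5% under mild imbalance. Reaching 10% or more takes a normal reference together with the harshest size pattern. The ICCs above 0.01 and the exact cluster sizes are assumptions, and the count of 20 is contradicted within the article.

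What remains is that the article presents these methods as the solution and extends them to all correlated outcomes. Under the imbalance it describes, every conventional version examined rejects too often. The size depends on the version; the direction does not.

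**Conclusion.** The point holds in conditional form. With 20 randomised school clusters of unequal size and clustering at that level, conventional versions of the named methods would test at about 6% to 10% at nominal 5%, and just under 11% at most in the settings tried. By version: about 6%-8% for G/(G−1)-scaled errors with t(19), about 8%-11% for z-referenced sandwich errors, and about 6%-9% for REML or ML Wald z tests.

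This rests on ICCs of 0.01 to 0.10, of which the article gives only 0.01, and on size patterns deduced from the random assignment section. If the 30 clusters of the power statement and Table 3 were correct, the range would be about 5%-7%.

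The unstated clustering level is a separate and potentially larger matter. Clustering on the 60 CBCCs instead of the 20 school clusters gave 8.8%, 14.0% and 17.4% at assumed ICCs of 0.01, 0.03 and 0.05. The inflation described here is what would remain after that is settled.

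**What to change.** First reconcile the number of randomised school clusters: 20 in the random assignment section, 30 in the power statement and Table 3. Then add one statement to the analysis section, or confirm that the analysis plan already contains it:

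- Inference is made at the level of the randomised primary school cluster.
- A few-cluster method is used: REML mixed models with Kenward-Roger or Satterthwaite degrees of freedom, or bias-reduced (CR2) cluster-robust errors with Satterthwaite degrees of freedom.
- For the primary outcomes, a permutation test that reassigns school clusters within traditional-authority strata serves as a check.

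The cost is a software option and a sentence or two. Confidence intervals become about 7% wider than with a normal reference (2.101/1.960 = 1.07 for 18 degrees of freedom), with a corresponding small loss of power.

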### Heterogeneity of impact

The large dataset will allow for extensive subgroup analyses, including gender, age and geographic characteristics. The impacts of preschool feeding may be quite heterogeneous and context specific [24, 25]. School meals, for instance, have been associated with marked improvements in school participation of girls in rural areas where there are large gender disparities in access to education [26]. Furthermore, smallholder farmers targeted by the programme are mostly female.

### Cost-effectiveness

Cost data will be collected retrospectively following an ingredients approach using a semistructured questionnaire. The survey will be based on a standardised costing framework capturing capital (fixed) and recurrent costs incurred at the school level. The questionnaire will also cover both cash and in-kind contributions and will be used to estimate both financial and economic costs. Financial costs capture actual expenditures in terms of programme implementation on an annual basis. Economic costs included the opportunity costs of community members, teaching staff and other stakeholders involved in the intervention provision. Opportunity costs of preschool staff and community members will be calculated using local pay scales. Capital costs will be annuitised over the useful life of all relevant school-level assets using a discount rate of 3% as per World Bank recommendations. Annuitisation enables an equivalent annual cost to be estimated and reflects the value in-use of capital items, rather than reflecting when the item was purchased. Process and output data covering the adequacy of the service delivery will be collected from monitoring visits on a quarterly basis using standardised data collection forms. Output data will be combined with the costs to provide estimates of cost-efficiency metrics, including costs per beneficiary, kilocalories, iron, and vitamin A delivered. Sensitivity analysis will be undertaken to account for uncertainties in the economic evaluation. The figures obtained in this way will then be compared to figures calculated for other interventions.

### Data collection

The enumerators will be recruited from Chancellor College, University of Malawi and trained for the baseline survey. Each team, led by a supervisor and assisted by community leaders, will conduct household listings and sampling in each enumeration area. The data collection will be undertaken using electronic tablets. Data collection will be reviewed daily by a team supervisor and inconsistencies clarified. Dietary assessment will be undertaken by trained and supervised enumerators using the interactive 24-h recall method. Prior to the recall interview, caregivers will be briefed on the purpose and methods of interview. The interview will be conducted using visual aids to assist in estimating portion sizes of the foods consumed. The 24-h dietary assessment will be repeated on nonconsecutive days for a subset of households (approximately 20%) to obtain estimates of usual intake [27]. Anthropometry collection will include measurements of children’s height and weight. Height or length will be measured to the nearest 0.1 cm using portable fixed base stadiometers and weight will be measured to the nearest 0.1 kg using electronic scales. The height and weight measures will be assembled and placed on a level surface. In the absence of a level ground in the household, a suitable place will be identified for the measurement in the community. Training on the MDAT will be provided to all supervisors and enumerators by trained staff from the College of Medicine, Malawi. During the MDAT training all enumerators will be reviewed for consistency and reliability.

## Discussion

Early childhood development programmes are considered as the most cost-effective form of human capital investment compared to any subsequent schooling interventions [4]. Emerging evidence highlights the potential additive and synergistic effects combining ECD, and nutrition [6, 7], and agriculture and nutrition [3]. Combining these three sectors may lead to substantial gains in cost, efficiency and effectiveness; however, there is a need to rigorously assess these potential synergies.

This paper describes the design for a CRT of a preschool-feeding-based intervention linked to smallholder agricultural and community engagement. As far as we are aware, it is the first to explicitly examine (from a food systems perspective) the simultaneous impact of a preschool meals programme on dietary choices, alongside outcomes in the nutritional, child development and agricultural domains. As the intervention is complex, the scope of this theory-based evaluation includes measurement of a range of outcome and process metrics across multiple disciplines. The data collection requires multisectoral expertise in the survey teams, including measurements of dietary intake, anthropometry and child development, alongside expenditure and other socioeconomic-related dimensions.

### Trial status

The first participant was enrolled on 7 September 2015. Data collection for the last of 120 participants will be completed by December 2016 (see the SPIRIT Checklist figure (Additional files 1 and 2)) (Fig. 4).

## Abbreviations

ANCOVA: Analysis of covariance
CBCCs: Community-based childcare centres
CBO: Community-based organisation
CRT: Cluster randomised trial
DDS: Dietary Diversity Score
DID: Difference-in-difference
ECD: Early Childhood Health and Development
FVS: Food Variety Score
HANCI: Hunger and Nutrition Commitment Index
HAZ: Height for age z-score
HH: Household
IRI: Interactive radio instructions
IYCF: Infant and Young Child Feeding
MDAT: Malawi Development Assessment Tool
MDES: Minimum detectable effect size
NEEP-IE: Nutrition Embedded Evaluation Programme Impact Evaluation
OFSP: Orange-fleshed sweet potato
SUN: Scaling Up Nutrition
TA: Traditional Authority
WALA: Wellness and Agriculture for Life Advancement
